#### Neuroimaging Data

The preprocessing of the structural and functional data will be performed using standard routines of the Statistical Parametric Mapping software (SPM12) [75] within MATLAB [67]. In the first step, lesions are delineated on T2-weighted (fluid-attenuated inversion recovery) or T1*-weighted (T1-weighted magnetization-prepared rapid gradient-echo sequence) images. In the second step, the raw data will be preprocessed including the following steps: realignment, slice timing, coregistration, normalization, and spatial smoothing. This step includes the lesion correction during the normalization process to ensure accurate spatial alignment across subjects, using standard delineation and lesion correction methods [76-78]. In the third step, first-level analysis will be conducted using a general linear model including the following 8 task regressors: 4 regressors for each condition (ie, LE, LC, object condition, and object control condition) in the encoding phase and 4 regressors for each condition (ie, LE, LC, object condition, and object control condition) in the retrieval phase. These regressors will be modeled using a delta (stick) function for the encoding phase (to best account for phasic changes in the neural response to the target set) and a boxcar function for the retrieval phase. Besides brain activation, we also plan to analyze functional connectivity within the frontal-parietal networks or ascending reticular activating system. For the diffusion tensor imaging data, fractional anisotropy, axial or radial diffusivity, mean diffusivity, and so forth will be used to analyze differences in structural connectivity.

For the retrieval phase of the working memory task, the mean reaction time for target and nontarget probes will be calculated for all the 4 task conditions. Accuracy will be calculated for each condition as a percentage of correctly identified probes. Presentation (version 23.0; Neurobehavioral Systems, Inc) [65] will be used for calculating these performance parameters. Further analysis steps will be conducted using SPSS Statistics (version 28.0.0.0; IBM Corp) [66] and MATLAB (R2024a) [67], for example, to compare the performance parameters of the task conditions between the PSD and non-PSD group, for example, multifactor ANOVA.

## Results

This study was funded in December 2023. The recruitment of patients was initiated in June 2024 and will continue until September 2025. As of May 2025, 15 patients with stroke have been included. Data acquisition will continue until December 2025. Data analysis will commence at the beginning of 2026, and study findings are expected to be published in summer 2026.

## Discussion

Here, we present the protocol of a longitudinal study (RECOVER) designed to investigate both short-term and long-term effects of PSD on cognitive impairment and recovery in patients with stroke. PSCI is assessed using a multimodal approach that includes a multicomponent digital neuropsychological assessment and task-based fMRI at 3 time points: during the acute (prior PSD development) phase, the postacute phase, and at the 3-month follow-up.

Prior behavioral studies showed significantly poorer cognitive outcome (eg, in global cognition or memory decline) in both patients with stroke with PSD and without PSD compared to healthy controls [1,24,33]. Thus, a clear distinction between “stroke-related” and “PSD-related” cognitive impairments has not been established so far.

Brain neuroimaging studies using structural MRI reported dysconnectivity within the cortical-subcortical systems, for example, reticulo-thalamo-cortical network [1,13,79] in patients with delirium. fMRI studies using resting state have further revealed disrupted connectivity in dorsal-prefrontal and subcortical networks in patients with delirium (compared to healthy controls). These alterations may be linked to core delirium symptoms, such as disorientation, altered arousal, attention deficits, or disturbances in the sleep-wake cycle [1,13,16,28,30,80,81].

Memory is a fundamental aspect of human cognition and a frequently affected domain in patients with stroke with PSD and without PSD [22]. However, memory impairments may not be detectable during resting-state fMRI [31]. Unfortunately, task-based fMRI studies that allow for the direct assessment of memory functions are currently very limited. To date, only 1 fMRI study has investigated this challenging area, reporting no significant association between delirium and brain region activity [32]. However, this study raises methodological concerns due to the absence of a control group and the use of an infeasible working memory task. Further research is therefore needed, alongside the development of an adequate and reliable assessment of working memory during fMRI.

Finally, there remains a notable gap in the literature regarding appropriate methods for studying PSD and related cognitive outcomes. This gap has been addressed by this longitudinal study protocol, which includes 3 measurement points and 2 groups of patients with stroke, PSD, and non-PSD (control), to assess PSCI. We followed a multicomponent assessment strategy for the neuropsychological assessment and introduced a suitable digital tablet app tailored for both patients with stroke with PSD and without PSD. This partly tablet−based neuropsychological assessment enables the generation of additional neuropsychological parameters, such as time in air or time on surface [42,74], which may help to detect patients with PSD at an early stage.

In addition, we present an extended (ie, verbal and visual items) and modified version of a well-known working memory task (Sternberg task) [58-61] to examine patients with stroke with PSD and without PSD. This study design enables the direct assessment of memory functions at both the behavior level via neuropsychological testing and advanced parameters derived from digitalized tests, and at the brain level via task-based fMRI, where patients actively perform the working memory task during scanning. Therefore, we can map the neural correlates of working memory functions and conduct brain-behavior correlation analyses. Additionally, this comprehensive longitudinal design, involving 2 patient groups (PSD and non-PSD), may allow us to differentiate between stroke-related and PSD-related cognitive impairments. Moreover, we aim to contribute preliminary insights toward developing protective and prognostic tools that support the early detection and treatment of PSD, ultimately helping to improve long-term cognitive recovery in patients with stroke.

The findings and experience gained from this proof-of-concept protocol will serve as early, preliminary investigation and provide essential groundwork for the design and implementation of future multicenter studies with a larger sample size. This protocol represents a first step toward expanding previous knowledge and improving the understanding of the contribution of PSD to long-term cognitive impairment after stroke.

These early findings from the proof-of-concept study hold promising clinical implications for the diagnosis and treatment of PSD, with further research required to validate these results on a larger scale. A more profound understanding of the cognitive dysfunctions associated with PSD could significantly influence clinical decision-making and rehabilitation strategies. Recognizing PSD as a distinct clinical condition characterized by specific patterns of cognitive impairment could help clinicians differentiate it from typical poststroke cognitive dysfunction. Specifically, the early identification of PSD-related cognitive deficits may enable the timely initiation of targeted, high-intensity cognitive rehabilitation, including domain-specific interventions such as those focused on attention, memory, and executive function. This approach has the potential to guide the development of individualized care plans tailored to patients’ needs, prevent long-term cognitive decline, and promote optimal cognitive recovery.

However, this study protocol has several limitations. First, our study population consisted of patients with stroke with mild-to-moderate symptoms (NIHSS ≤15) and excluded patients with stroke with more severe stroke symptoms, particularly those with a GCS score ≤8, as well as patients with aphasia, which limits the generalizability of our findings to the broader population with stroke. However, patients with global aphasia are often unable to comprehend test instructions or follow simple requests (eg, “close your eyes”), making the assessment of cognitive functions, such as memory functions, extremely challenging, time-consuming, and often frustrating for the patient. Patients with a GCS score ≤ 8 have typically significantly reduced levels of consciousness, making a reliable cognitive assessment not possible. Second, the sample size is 40. Although this proof-of-concept study is underpowered, it is essential for gathering preliminary data and assessing feasibility. Insights gained will provide critical groundwork for designing larger, adequately powered studies in the future. Another important limitation of our study protocol is the variable timing of assessments, especially for S2, which is scheduled within a broad window of 5-14 days post stroke. These flexible time windows were intentionally selected to accommodate clinical realities and to minimize dropout rates and missing data. Regarding S2, this variability is driven by clinical realities, including patient transfers on short notice, fluctuating medical conditions, limited MRI availability, and the unpredictable course of delirium recovery. Unfortunately, the MRI assessment cannot take place during the acute phase of a delirium but only after partial recovery from delirium, a common problem in behavioral and neuroimaging studies on delirium or PSD. While this flexible scheduling approach enhances the feasibility of conducting comprehensive neuropsychological and imaging assessments in a population with acute stroke, it introduces potential confounding effects related to differences in the timing of measurements across patients. To mitigate this issue, we will incorporate the number of days post stroke as a covariate in our statistical analyses. Future large-scale studies should consider using more standardized normalization strategies to handle timing variability at S2, such as time normalization or statistical correction for nonlinear recovery effects in mixed effects models.

Another concern in our multimodal longitudinal study is the increased risk of participant dropout compared to cross-sectional studies. This risk is particularly pronounced among patients with PSD, given the association between PSD, lower quality of life, and higher mortality rates, which may lead to a higher than anticipated dropout rate. To address this, we have implemented several mitigation strategies. First, as described above, we have established predefined time windows to accommodate clinical realities within this vulnerable study population while prioritizing patients’ well-being. Assessments are adjusted within predefined time windows based on the patient’s condition, balancing protocol adherence with clinical care and comfort. Second, both neuropsychological and MRI assessments include opportunities for breaks or pauses to manage patient fatigue or distress. Third, when the patient’s condition or transfer prevents in-hospital assessment, we offer follow-up visits at patients’ homes or rehabilitation centers. Collectively, these measures enhance feasibility and data completeness while ensuring patient safety and comfort.

This study protocol involves important ethical considerations due to the vulnerability of patients with acute stroke, particularly those experiencing PSD. Ensuring ethical responsibility and patient safety is of the utmost importance. In an effort to minimize the burden on participants, both neuropsychological testing and MRI sessions are kept as brief as possible and can be paused or rescheduled based on the patient’s condition. Testing is immediately halted if any signs of distress or fatigue arise. Throughout the entirety of the procedures, the presence and attentiveness of clinical staff are maintained. The inclusion of cognitively vulnerable patients is ethically justified, as this group is often underrepresented in research. However, their participation is carefully balanced with stringent safeguards to prevent any undue burden on their health or recovery. The presented protocol is critical to provide a comprehensive framework for assessing cognitive outcomes tailored to the challenges of evaluating older patients with stroke with and without PSD.

While this was beyond the scope of this proof-of-concept study, future studies should be initiated as multicenter trials to enhance the generalizability and robustness of the findings. Increasing the sample size will be essential to achieve adequate group sizes and improve statistical power. Additionally, balancing groups according to key variables, such as lesion location or stroke severity, would strengthen the validity of comparisons.

Another important aspect is the consideration of the amount of cognitive rehabilitation on PSCI. Unfortunately, this was beyond the scope of this study, and this protocol includes only documentation of whether rehabilitation was received and its duration. A detailed evaluation of the effect of cognitive rehabilitation impact on long-term outcomes should be addressed in future studies. Another consideration would be extended follow-ups, for example, after 6 and 12 months, to better capture cognitive trajectories.

This protocol represents a proof-of-concept study designed to systematically and comprehensively examine cognitive functions in critically ill patients with acute stroke with and without delirium. It combines comprehensive neuropsychological testing with a multimodal MRI protocol, including digitalized assessments and task-based functional MRI. By addressing a significant clinical gap and using innovative methodologies, this study lays essential groundwork toward larger, adequately powered studies.

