**Figure 1. F1:**
[figure not shown]
Overview of the RECOVER (Cognitive Recovery After Poststroke Delirium) study procedures. DSM-5: *Diagnostic and Statistical Manual of Mental Disorders, Fifth Edition*; DTI: diffusion tensor imaging sequence; FLAIR: fluid-attenuated inversion recovery sequence; ICDSC: Intensive Care Delirium Screening Checklist; MPRAGE: T1-weighted magnetization prepared rapid acquisition with gradient echoes sequence; MRI: magnetic resonance imaging; NIHSS: National Institutes of Health Stroke Scale; S1: session 1; S2: session 2; S3: session 3; T2*: T2-weighted echo planar imaging sequence; WM: working memory.

The three measurement points are as follows:

S1 during the acute phase poststroke (≤48 h after hospital admission; ≤96 h after stroke onset and before PSD development)S2 during the postacute phase poststroke (5‐14 d poststroke, depending on delirium recovery)S3 follow-up at 3 months poststroke (approximately 90 d poststroke)

Patients with stroke will be admitted to the Stroke Unit where a screening visit will be conducted, including a review of the inclusion and exclusion criteria. Following the review, written informed consent will be obtained from the patient or, if applicable, the legal guardian. Once consent has been obtained, the patient will be enrolled in the RECOVER study.

Each measurement (S1-S3) consists of a clinical examination, a multicomponent neuropsychological testing, and an MRI protocol. The MRI protocol is designed to acquire both structural (anatomical) data, as well as functional data (see the *Neuroimaging Protocol* section for more details). The clinical examination includes the National Institutes of Health Stroke Scale (NIHSS) [35] and will take approximately 15 minutes. The multicomponent neuropsychological assessment and the MRI scan (including positioning of patient) will each require 45‐60 minutes. A more detailed description is provided in the *Neuropsychological Assessment and Clinical Scores* section. S1 and S2 will be conducted as in-patient measurements, and the S3 3-month follow-up measurement will be conducted as an out-patient measurement.

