During the course of the longitudinal study, in particular before S2, the cohort of patients with stroke will be subdivided into 2 groups, those with PSD and those without (non-PSD). Delirium screening using the ICDSC [32] will be conducted throughout hospitalization to identify the onset and duration of delirium. To ensure timely detection of delirium onset and recovery, assessments will be performed every 8 hours. A diagnosis will be made according to the DSM-5 criteria by an independent neurologist, who will review the clinical course alongside the ICDSC data. Delirium recovery is defined as 3 consecutive negative ICDSC screenings.

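### The S2 recovery condition is stated in two ways, so S2 group differences can reflect delirium that is still present, which the planned days covariate does not address

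*Protocol article*

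**What the plan says.** Methods, Study Design and General Procedures, places S2 at 5 to 14 days after stroke, "depending on delirium recovery". The same section states: "Delirium recovery is defined as 3 consecutive negative ICDSC screenings". On the ICDSC it adds that "assessments will be performed every 8 hours" during the hospital stay. It also makes imaging part of every session: "Each measurement (S1-S3) consists of a clinical examination, a multicomponent neuropsychological testing, and an MRI protocol".

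The limitations paragraph of the Discussion returns to S2 and says that "the MRI assessment cannot take place during the acute phase of a delirium but only after partial recovery from delirium". Partial recovery is not defined there or elsewhere. The paragraph attributes the wide S2 window to several causes, among them "limited MRI availability, and the unpredictable course of delirium recovery", accepts that this can confound, and offers one remedy: "we will incorporate the number of days post stroke as a covariate in our statistical analyses". Correction for nonlinear recovery is left to future studies.

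Table 1 lists the ICDSC among the measures taken at S2. The primary endpoint (global PSCI) and the secondary endpoints (domain-specific PSCI) are both at S3, the 3-month visit.

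**The concern.** A PSD patient who is improving but still screens positive meets the Discussion's condition and fails the Methods' definition. Whether that patient has an S2, and what that S2 measures, depends on which text the site follows.

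The distinction matters because delirium symptoms and S2 measurements overlap. The article itself names attention deficits, confusion and disorientation as features of delirium, and Table 1 measures attention, orientation and memory at S2. If some PSD sessions precede defined recovery, the S2 comparison mixes cognition during delirium with cognition after it. S2 is the only planned session after delirium onset and before 3 months. The short-term aim, the third objective (separating PSD-related from stroke-related impairment) and any S2 fMRI group comparison therefore depend on what it captures.

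Timing is a second, smaller matter. Only PSD patients can have S2 delayed by delirium, so days since stroke may be related to group.

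**Working it through.** **1. The texts side by side**

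| Place | Condition for S2 in a PSD patient |
|---|---|
| Methods | Timed by recovery, defined as three negative screens in a row; at 8-hour intervals, first to third negative = 2 × 8 = 16 hours |
| Discussion | MRI after partial recovery, undefined |

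The second is looser than the first, and the MRI belongs to S2. There is no power or sample-size figure in the article to reproduce.

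**2. Does the days covariate remove residual delirium?**

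Simulation with 4,000 runs, 20 per group (from the article) and residual SD 1. The rest is assumed: no lasting PSD effect, non-PSD scanned uniformly on days 5–10, PSD scanned 0 or 4 days later, linear recovery of 0.1 SD per day, and an average residual-delirium deficit δ in the PSD group. As a scale for δ, 6 of 20 PSD patients each 1 SD worse gives 6/20 × 1 = 0.3 SD.

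| δ (SD) | Adjusted estimate, no lag | Significant, no lag | Adjusted estimate, 4-day lag | Significant, 4-day lag |
|---|---|---|---|---|
| 0 | 0.00 | 5% | 0.00 | 5% |
| 0.3 | −0.30 | 15% | −0.28 | 8% |
| 0.5 | −0.50 | 34% | −0.50 | 14% |
| 0.8 | −0.80 | 67% | −0.80 | 30% |

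The deficit passes through. The lower rates with a lag come from lost precision, not from less bias.

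**3. Does the covariate remove stroke-stage differences?**

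Same set-up with δ = 0 and a 4-day lag. With linear recovery, bias goes from +0.39 to 0.00 SD. With exponential recovery, it goes from +0.54 to −0.06 SD. So mostly yes, when scan days overlap. The standard error rises from 0.32 to 0.55.

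**4. What precision does it cost?**

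For equal groups, variance inflation = 1/(1 − r²) = 1 + (gap/2)² / (mean within-group variance of day). A uniform spread over k whole days has variance (k² − 1)/12. All day ranges are assumed.

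- PSD 6–14, non-PSD 5–10: gap 2.5; variances 6.67 and 2.92, mean 4.79; 1 + 1.5625/4.79 = 1.33 (simulated 1.34).
- PSD 7–14, non-PSD 5–10: gap 3.0; variances 5.25 and 2.92, mean 4.08; 1 + 2.25/4.08 = 1.55 (simulated 1.58).
- PSD 8–14, non-PSD 5–8: gap 4.5; variances 4.00 and 1.25, mean 2.625; 1 + 5.0625/2.625 = 2.93 (simulated 3.00).
- Both groups 5–14: simulated 1.01.

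The standard error is thus multiplied by about 1.16 (√1.34) to 1.73 (√3.00) in the lagged cases.

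**5. Can the covariate absorb part of the PSD effect?**

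Here the PSD scan day is assumed to be day 5 or day 7 plus a delirium duration of 1–7 days (mean 4), with cognition falling 0.1 or 0.2 SD per day of delirium.

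- 0.1 SD per day: true deficit 0.1 × 4 = 0.40 SD; adjusted estimates −0.31 and −0.18.
- 0.2 SD per day: true deficit 0.2 × 4 = 0.80 SD; adjusted estimates −0.63 and −0.38.
- No duration effect: adjusted estimates 0.00 and −0.02, so no material distortion.

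The fitted day slope is 0.04 or −0.02 instead of 0.10, because day stands in for duration.

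**The case against.** The case against runs as follows. The three-negative rule sits in a paragraph about detecting the onset and duration of delirium, and nothing there makes it a precondition for S2. The partial-recovery sentence is in the limitations, concerns the MRI only, and explains why scanning in acute delirium is impossible. It is not written as a scheduling rule. Variable timing is openly disclosed and a covariate is promised. The endpoints are at S3, and the study calls itself underpowered and preliminary.

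Much of this stands. That recovery governs S2 is an inference from linking the S2 window to a term defined in the same section. Even so, the article uses that term one way in the Methods and describes a weaker state in the Discussion. Both statements are on the page, so this is not detail left to a fuller document.

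A reader might go further in three ways that the documents do not support:

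- **That PSD patients are systematically tested later.** No S2 dates by group are given. Transfers, medical condition and scanner access can affect either group, and delirium that clears before day 5 need cause no delay.
- **That the covariate fails for timing.** Step 3 shows that it removes most stroke-stage bias when days overlap. Its limits are residual delirium, for which it was not offered, and scan days driven by delirium duration.
- **That variance triples.** That figure needs nearly separate day ranges; the mildest lagged case gives 1.34.

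**Conclusion.** The inconsistency holds and should be resolved. As written, some PSD sessions at S2 may precede the article's own definition of recovery, and the one named adjustment does not separate ongoing delirium from impairment after it. Under the assumptions shown, an average residual deficit of 0.3 to 0.8 SD biases the S2 contrast by about that amount. The share of such sessions and the size of the deficit are unknown, so these figures illustrate and do not predict.

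The timing part is secondary. If delirium does delay S2, the covariate costs precision (variance about 1.3 to 3 times under assumed day ranges). If delirium duration itself affects cognition, it may also absorb part of the PSD effect.

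A reader might infer that the main result is at risk. It is not: the primary and secondary endpoints are at S3, and the harm is limited to S2 short-term, fMRI and differentiation analyses.

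**What to change.** 1. Reconcile the Methods and the Discussion so that one S2 recovery condition is stated throughout, for the MRI and for the neuropsychological testing. Which condition applies is for the investigators to decide.
2. Classify each PSD patient's S2 as recovered or not recovered by the Methods definition, using the 8-hourly ICDSC and the ICDSC at S2. Where a transfer leaves too few screens to tell, label the session undetermined.
3. Report the S2 PSD versus non-PSD comparison twice: for all sessions, and for recovered sessions only.
4. Report the number and delirium duration of PSD patients not recovered at S2 or without an S2.
5. Report S2 day by group. State alongside the days-adjusted results that the covariate can cost precision and may absorb part of a delirium-duration effect.

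The cost is protocol wording and some tabulation, with no new data collection, and steps 2 to 5 also apply to sessions already completed. The downside is that the recovered-only comparison is smaller and omits prolonged delirium, which is why it should stand beside the all-sessions result and not replace it. Moving non-PSD visits later to match is not asked for, since S2 is an in-patient session and transfers occur at short notice.
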